### Statistical data analysis

We will use generalized linear mixed models throughout the analysis to account for multiple observations per patient and shared characteristics (correlation) between geographical clusters [60]. Models will be adjusted for patient age, sex, case-mix group [61], number of patient-days and hospital type. Using intention to treat, clusters will be analyzed according to their randomized cross over time from control to intervention period, with preintervention period data being excluded as washout. Calendar time will be included as a fixed effect for each step to account for secular trends. We anticipate using logistic regression (via a logit link) for binary outcomes (inpatient mortality, 30-day readmission, 30-day mortality), Poisson regression for count variables (e.g. number of tests) and linear regression models for continuous outcomes (e.g. length of stay). A p-value < 0.05 will be considered statistically significant. We will use complementary data from our surveys, data and field notes collected through the implementation process tracking tool, and qualitative data collected during the facilitated utilization data review sessions to help interpret site-specific results.

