
### Study design

This multicenter, quasi-experimental stepped-wedge cluster randomized trial [51] will assess whether a multicomponent intervention bundle can reduce the number of target routine laboratory tests ordered in hospitalized medical patients. Implementation of the intervention bundle will be guided by the Knowledge to Action cycle [52], where we will understand the local context, assess local barriers and facilitators, and select and tailor our intervention tools. We will use the RE-AIM (Reach, Effectiveness, Adoption, Implementation and Maintenance) framework [53, 54] to evaluate the intervention bundle and the National Health Service (NHS) Sustainability model to plan for sustainment [55].

The study will first conduct a feasibility assessment of the intervention bundle tools over a 16-week pilot period at one site. The pilot period will provide an opportunity for testing the intervention tools and developing implementation strategies. After the pilot, each cluster will enter the implementation stage in 12-week steps (Fig. 1) in a random order determined by computerized random number generation. Each cluster will contain approximately 2 hospitals, loosely grouped based on geographical proximity. A cluster will be eligible to enter randomization for implementation once local data infrastructure is complete. The initial four weeks of implementation will serve as the pre-intervention period, which will be followed by an 8-week intervention period. The final four weeks of the intervention period for one cluster will overlap with the pre-intervention period of the following cluster (Fig. 1).

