**Fig. 1 Fig1:**
[figure not shown]
Stepped-wedge cluster randomized trial study design for the intervention bundle. C= Control, Pre= Preintervention period, INT= Intervention period

During the pre-intervention period, we will finalize multidisciplinary implementation teams including nurse managers and educators, ward directors, physicians, resident physicians, and medical students at each site. Local implementation teams will provide information on local barriers and facilitators which will allow for selection and tailoring of intervention tools. They will receive virtual implementation support by the research team and the Patient Advisory Council to adapt and deliver intervention bundle tools within local context. Different intervention tools may be used at each site depending on local context and adapted to local barriers and facilitators. Each site will receive at least one tool for healthcare provider engagement and one for patient engagement. All site-specific modifications of intervention tools will be noted in our implementation process tracking tool (Fig. 2). Members of implementation teams will also complete a combined survey to assess readiness for implementation (based on the Ready, Set, Change! Decision support tool [56]) and determine overall climate of sustainability and strategies to enable sustainability of the intervention (based on NHS Sustainability survey [57]) (Additional file 3).

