### Sample size calculation

Based on administrative data, we estimate a mean of three target laboratory test orders per patient at baseline, and an average of 100 patients per site per day on the medical wards. We believe that a 10% reduction in mean number of target test orders per patient-day is clinically important. With 16 participating sites, 8-week intervention periods, and an intra-cluster correlation of 0.1 based on our prior work or even as high as 0.2 to account for geographical clustering, we will have the ability to detect a difference of 10% in our primary outcome with greater than 90% power (2-sided alpha of 0.05) [59].

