Our study is also one of few studies that includes patient engagement embedded in every aspect of the research and includes co-designed intervention tools that will be implemented. This trial will contribute to the understanding of how to apply the science of Knowledge Translation to de-implementation [69], including delivery of Audit and Feedback reports, design of patient engagement strategies, and evaluation of tailored pragmatic multicomponent strategies. To the best of our knowledge, this is one of the largest planned de-implementation trials focusing on reducing redundant use of routine daily laboratory testing in hospitals. Results of the study have the potential to improve the quality of care for hospitalized patients. Lessons learned will help inform future implementation of other interventions in hospitals in general, a treatment setting that deals with high-cost and high-acuity care [70]. Given the lack of evidence on why and how implementation strategies work, our complementary data to understand local contextual determinants will advance the science of implementation.

Results of our study will be disseminated to healthcare providers and researchers through presentations at national and international conferences and open-access publications in peer-reviewed journals. Furthermore, we plan to have a cross-sectoral meeting with interested policymakers, healthcare providers and patient participants after the end of the study to disseminate experiences and findings. We will also conduct a press release after publication to share information with the public. We will include project metadata in the supplementary appendix of published articles.

Given the stepped-wedge design, a notable limitation is potential confounding due to temporal trends as more clusters are exposed to the intervention with study progress [58]. To counter this, we will use randomization to determine the sequence of cluster entry into intervention. In this study, hospital is the unit of randomization, therefore contamination with physicians and medical trainees working in multiple hospitals is possible. The study will report on the effect of this intervention in a population of hospitalized adult medical patients in a single province in Canada, as such, results may not be generalizable to other patient populations and settings.

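### As written, the primary mixed model has no cluster-by-period term, so its 5% test holds only if all clusters follow exactly parallel time courses

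*Protocol article*

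**What the plan says.** All references are to the protocol article.

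- **Correlation (Statistical data analysis).** The plan uses "generalized linear mixed models throughout the analysis to account for multiple observations per patient and shared characteristics (correlation) between geographical clusters".
- **Time (same section).** "Calendar time will be included as a fixed effect for each step to account for secular trends". This is one time course shared by all clusters.
- **Covariates (same section).** "Models will be adjusted for patient age, sex, case-mix group [61], number of patient-days and hospital type". Hospital type is a fixed covariate and does not stand in for a hospital effect.
- **Outcome model (same section).** The primary outcome is a count, handled by "Poisson regression for count variables (e.g. number of tests"), with p below 0.05 as the criterion.
- **Sample size calculation.** It gives one ICC, 0.1 and possibly 0.2, and no correlation between periods. It assumes "an average of 100 patients per site per day on the medical wards".
- **Randomised unit.** Study design has clusters entering in random order: "Each cluster will contain approximately 2 hospitals, loosely grouped based on geographical proximity". The limitations paragraph of the Discussion states: "In this study, hospital is the unit of randomization".

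**The concern.** A stepped wedge gets most of its information from change within a cluster over time. A model with one constant random intercept per cluster treats two patient-days in that cluster as equally correlated whether they are a week or a year apart. Any local movement in the testing rate that other clusters do not share is then averaged over thousands of patient-days and counted as almost noise-free evidence.

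The protocol gives reason to expect such movement. Baseline, rollout and follow-up together run well over a year, and implementation is local: "Different intervention tools may be used at each site depending on local context". At stake are the primary confidence interval and p-value. A local fluctuation unrelated to the bundle could be declared a significant effect in either direction.

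**Working it through.** **Inputs from the protocol.** 100 patients per site per day; baseline mean 3 (read as per patient-day, like the outcome); target reduction 10%, so 0.3; ICC 0.1 to 0.2; 8-week periods; 16 sites; two-sided 0.05; about 2 hospitals per cluster.

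**Assumptions.** Residual variance of one patient-day 3 (Poisson); within-patient inflation DE of 1 to 4; 16/2 = 8 clusters; 14 equal periods (3 baseline, 8 rollout, 3 after); linear approximation on the mean scale; CAC over a range.

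**1. Size of a cluster-step.** m = 2 × 100 × 56 = 11,200 patient-days.

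**2. SE from the model as written.** Cluster variance = 3 × 0.1/0.9 = 0.333. Sampling variance of a cluster-period mean e = 3 × DE/11,200 = 0.00027 (DE 1) or 0.00107 (DE 4). Generalised least squares with fixed period effects and one random intercept per cluster gives SE 0.006 to 0.012.

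**3. The plan's own figure.** 0.3/0.012 = 25 standard errors, so power is above 99.9%. This agrees with the stated power of more than 90%. Parallel-group calculations with a design effect give only 11–19%, so the stated power rests on the within-cluster comparison over time.

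**4. The same model when clusters drift.** Let the cluster variance split into a constant part (share CAC) and a cluster-period part (share 1 − CAC). Then, to the digits shown,

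(true SE / model SE)² = 1 + (1 − CAC) × [ICC/(1 − ICC)] × m/DE,

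type I error = 2Φ(−1.96/ratio).

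The outcome SD cancels from the ratio, and dropping the extra baseline and follow-up periods leaves the ratio unchanged. At ICC 0.1 the constant is 11,200/9 = 1,244; at ICC 0.2 it is 11,200/4 = 2,800. Example (ICC 0.1, CAC 0.95, DE 4): 1 + 0.05 × 1,244/4 = 16.6; ratio 4.1; type I error 63%.

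| CAC | Drift SD at ICC 0.1 (% of mean 3) | Ratio, ICC 0.1 | True SE, ICC 0.1 | Type I, ICC 0.1 | Type I, ICC 0.2 |
|---|---|---|---|---|---|
| 1 | 0 | 1.0 | 0.006–0.012 | 5% | 5% |
| 0.999 | 0.018 (0.6%) | 1.1–1.5 | 0.009–0.014 | 9–19% | 13–31% |
| 0.99 | 0.058 (1.9%) | 2.0–3.7 | 0.022–0.024 | 33–59% | 49–72% |
| 0.95 | 0.129 (4.3%) | 4.1–8.0 | 0.048–0.049 | 63–81% | 74–87% |
| 0.90 | 0.183 (6.1%) | 5.7–11.2 | 0.067–0.068 | 73–86% | 82–91% |

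Ranges run between DE 4 and DE 1. Drift SD = √[(1 − CAC) × 0.333].

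**5. Where the problem shrinks.** With DE 10 at ICC 0.1, the ratio is 1.5 (19%) at CAC 0.99 and 3.7 (59%) at 0.90. With ICC 0.01, DE 4 and CAC 0.95: 1 + 0.05 × (11,200/99)/4 = 2.4, ratio 1.6, type I error 21%.

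**6. Omitting a constant hospital intercept.** If both hospitals of a cluster switch together and are of equal size, the ratio is 1.00 and type I error 5%. If hospitals switch separately, the ratio in the layout tried is 9.9 to 24 (84–94%) for assumed between-hospital variances of 0.05 to 0.30, even at CAC 1. The exact figure depends on how the hospitals are paired.

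**7. Power once a cluster-by-period term is in the model.** 8 clusters, 9 periods, total variance 3, DE 4; z-test, with a t-test on 6 df in brackets:

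| CAC | ICC 0.1 | ICC 0.2 |
|---|---|---|
| 0.95 | about 100% (99%) | 99% (93%) |
| 0.90 | 99% (93%) | 84% (68%) |
| 0.80 | 84% (69%) | 56% (37%) |

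**The case against.** The strongest reply has four parts.

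- **The sentence states a purpose and is not a closed list of random effects.** The article is condensed, and an unseen analysis plan may add terms. This stands as a limit: a reader might infer that the trial will certainly fit only these two sources of correlation, and the document does not say so. But the section does set out the correlation, the common time effect, the distribution and the threshold. A model built from it as written has the weakness described.
- **The inflation depends on a CAC that the document never gives.** This also stands. A reader might infer that the standard errors are known to be several times too small. They are not: at CAC 1 there is no inflation. Yet the drift needed is small, about 2% of the mean at CAC 0.99.
- **Adjustment for case mix and calendar step already removes some drift.** Partly true, and the figures above allow for none of it. Common step effects cannot remove movement peculiar to one cluster, and patient covariates cannot remove changes in local ordering practice.
- **A missing hospital intercept does no harm.** Correct under Study design if paired hospitals cross over together and are of similar size. It fails if the Discussion's statement of the randomised unit is the true one.

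A reader might also go on to require a negative binomial model or a random intervention effect. The documents give no dispersion figure and no figure for variation of the effect between sites, so neither is pressed here.

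**Conclusion.** The point holds in conditional form. The model as described gives a valid primary test only if every cluster follows the same time course apart from the intervention. With 11,200 patient-days per cluster-step and an ICC of 0.1 to 0.2, even slight separate drift makes the nominal 5% level misleading: roughly a third or more of null trials would reject at CAC 0.99, and most would at 0.95. These sizes rest on an assumed CAC, within-patient inflation of 1 to 4 and 8 equal clusters. They are smaller with stronger within-patient correlation or a much smaller ICC.

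The documents do not show that the primary p-value will be wrong. They show a stated model with no protection against an ordinary feature of this design. The contradiction over the randomised unit is definite, and it decides whether the hospital level matters as well.

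**What to change.** 1. Reconcile Study design and Discussion on whether single hospitals or clusters of hospitals are randomised, and state one unit.
2. State the primary model with random intercepts for the randomised unit and for hospital, plus a unit-by-period (or hospital-by-period) random effect.
3. Base inference on the number of randomised units, with a small-sample correction or a permutation test over the randomisation scheme.
4. Restate the power in Sample size calculation over a range of between-period correlations.

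The cost is protocol and analysis-plan wording, somewhat heavier computation, wider intervals and a less favourable stated power where CAC is low. At ICC 0.1 the z-test keeps above 90% power down to CAC 0.90 under the assumptions in step 7; at ICC 0.2 it does not. No new data are needed.

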### Costing analysis

We will compare costs of care and patient outcomes with and without implementation of the intervention bundle from the perspective of the publicly funded healthcare system. We will include costs of: (i) target laboratory tests with and without implementation of the intervention bundle using a cost per test or test group obtained from published reference median costs [62]; (ii) the index hospitalization (hospitalization where the implementation occurs) for each patient using micro-costing data [63] to provide a detailed cost per patient, including all resources consumed during the hospital stay such as direct and indirect nursing costs, surgery, ancillary services (physiotherapy, occupational therapy), and laboratory and drug costs; (iii) post-hospitalization healthcare costs over the 30-day period following discharge from hospital for the index hospitalization including: subsequent hospitalizations, emergency departments visits, ambulatory care, and urgent care costs. This will be done to estimate unintended downstream consequences of intervening on laboratory test use. We will present costs by category, and the differences in total costs will be calculated and compared to implementation costs. Our analysis will be a detailed cost consequence analysis, presented in conjunction with other outcomes.

## Discussion

As healthcare costs increase globally, we need context-specific de-implementation strategies to reduce low-value healthcare practices and integrate effective, evidence-based approaches. Our study is one of few implementation science studies that combines real-world operational change with a rigorous scientific evaluation approach to comprehensively study the de-implementation of the practice of repetitive use of routine laboratory testing in hospitals. Specifically, the study builds on intervention tools that have previously demonstrated success with reduction of redundant laboratory testing in hospitals [29, 30], and capitalizes on the momentum created by the current national campaign headed by Choosing Wisely Canada to ‘*Use Labs Wisely’ * [64].

While numerous studies have focused on reducing repetitive laboratory testing in hospitals, most are small, single institution efforts without clear plan for sustainability or scale [28, 65]. Our study is a robust effort to build upon prior work in a systematic manner that allows for scale and plan for sustainability. A recent systematic review on interventions to reduce repetitive ordering of low-value inpatient laboratory tests identified EMR and policy changes as the most effective and sustainable [28]. However, providers found the use of strict limitations and unavoidable pop-up alerts unfavourable. Moreover, focused EMR or policy changes are easier for laboratory tests that have clearly defined appropriateness criteria or re-testing intervals.. In contrast, the tests we focus on for our study are common tests with wide applicability, it is only their redundant use that is low-value [37, 66]. As such, our multicomponent intervention bundle which combines education, audit and feedback, EMR changes and patient engagement is novel in the area of repetitive laboratory test utilization and will contribute to our understanding of how the different elements can interact and contribute to reducing repetitive laboratory test utilization, while engaging and winning the favour of practising providers. Our study will be one of the few that has developed de-novo patient engagement tools in this field and will report on the evaluation of those tools as part of a multicomponent intervention bundle. In an era of increasing patient access to laboratory test results, patient engagement tools to empower and engage patients with appropriate use is timely.

While audit and feedback is a widely used strategy to improve professional practice and has been used as a component of other multimodal quality improvement studies, there exists considerable heterogeneity in the methodologies used [67]. The effectiveness of audit and feedback depends on baseline performance and method of delivery of the feedback [67]. In our study, we use an established framework of delivering audit and feedback (Calgary Audit and Feedback Framework) which has demonstrated prior efficacy [30, 38, 39]. This study will contribute towards building evidence around a specific method of delivering audit and feedback which can be reliably replicated and adapted based on evolving evidence. Hence our study will help advance the science of delivery of audit and feedback. In addition, our use of virtual facilitation for the group audit and feedback sessions to enable province-wide implementation will contribute towards evidence in the area of virtual application of facilitated audit and group feedback based on the Calgary Audit and Feedback Framework. A recent scoping review on virtual facilitation identified significant variability on reporting of virtual facilitation and lack of details on how it was conducted [68]. Our study will contribute towards literature in the development and evaluation of effective virtual facilitation to improve uptake of interventions, both through the application of virtual facilitation for implementation support, and for the facilitated audit and feedback sessions.

Our study is also one of few studies that includes patient engagement embedded in every aspect of the research and includes co-designed intervention tools that will be implemented. This trial will contribute to the understanding of how to apply the science of Knowledge Translation to de-implementation [69], including delivery of Audit and Feedback reports, design of patient engagement strategies, and evaluation of tailored pragmatic multicomponent strategies. To the best of our knowledge, this is one of the largest planned de-implementation trials focusing on reducing redundant use of routine daily laboratory testing in hospitals. Results of the study have the potential to improve the quality of care for hospitalized patients. Lessons learned will help inform future implementation of other interventions in hospitals in general, a treatment setting that deals with high-cost and high-acuity care [70]. Given the lack of evidence on why and how implementation strategies work, our complementary data to understand local contextual determinants will advance the science of implementation.

Results of our study will be disseminated to healthcare providers and researchers through presentations at national and international conferences and open-access publications in peer-reviewed journals. Furthermore, we plan to have a cross-sectoral meeting with interested policymakers, healthcare providers and patient participants after the end of the study to disseminate experiences and findings. We will also conduct a press release after publication to share information with the public. We will include project metadata in the supplementary appendix of published articles.

Given the stepped-wedge design, a notable limitation is potential confounding due to temporal trends as more clusters are exposed to the intervention with study progress [58]. To counter this, we will use randomization to determine the sequence of cluster entry into intervention. In this study, hospital is the unit of randomization, therefore contamination with physicians and medical trainees working in multiple hospitals is possible. The study will report on the effect of this intervention in a population of hospitalized adult medical patients in a single province in Canada, as such, results may not be generalizable to other patient populations and settings.

## Trial status

Pilot implementation since May 6th 2024.

## Data Availability

The final trial data set will be accessed by the study PI (AA), project team statisticians and data analysts. All administrative data used in this study are available from the provincial and institutional health authority data analytics sources and can be requested in accordance with institutional policies and procedures. All other data (including qualitative data) are available from the corresponding author upon reasonable request.

